### Statistical analysis

IMB SPSS Statistics 22.0 (IBM Corp., Armonk, NY, USA) will be used to process data and conduct a *t*-test, chi-square test, and correlation analysis. Analyses will be conducted based on an intention-to-treat approach, and two-sided with *P* < 0.05 will be considered statistically significant. Quantitative data accords with normal distribution will be described as mean ± standard deviation (*SD*), and qualitative data will be expressed as the number (percentage). Student’s *t*-test and the chi-square test will be employed to examine between-group differences in the baseline. The repeated measures ANOVA will be used to compare the scores for the six instruments, and the paired-samples *t*-test will be used to test for within-group differences. We will also conduct a correlation analysis to test the associations between variables in pre-program and post-program in each group. Structural Equation Model will be conducted to explore the interaction of the variables.

Furthermore, in order to elaborate on the meaning of the relationship between the mindfulness training and the outcome variables of mental state and quality of life among COVID-19 survivors, an analysis of mediator or moderator effects will be conducted and some more in-depth information about the research may be explained. We will use the hierarchical multiple regression analyses to test how or why some facets of mindfulness may take a role in our outcomes.

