## Background

Coronavirus disease 2019 (COVID-19), the infection caused by severe acute respiratory syndrome coronavirus 2 (SARS-CoV-2), was first reported on December 31, 2019. On March 11, 2020, the World Health Organization (WHO) declared the COVID-19 as a pandemic due to its rapid global spreading. Globally, there have been 122 536 880 COVID-19 cases and 2 703 780 deaths, particularly among vulnerable populations such as patients with chronic diseases and the elderly [1, 2]. As of 24:00 pm on March 22, 2021, China alone has resulted in 102 566 cases and 4850 deaths due to COVID-19 [3]. It can be seen that the mortality rate of COVID-19 has been declining recently, which means that more and more patients have been released from the hospital after being cured. Therefore, the focus has now been shifted to taking measures to rehabilitate COVID-19 survivors, including the restoration of their physical functions and psychological development.

Evidence suggests that this disease has psychological consequences on healthcare workers, students, psychiatric patients and general workers, especially for COVID-19 patients [4–13]. Immediately after the outbreak, a considerable proportion of patients with COVID-19 reported post-traumatic stress disorder (PTSD) (more than 33.0%), depression (60.2%), and anxiety (55.3%) symptoms in Shanghai, China [9]. In addition, a survey conducted in March, 2020 showed that 45.9% of patients had symptoms of depression, 38.8% had anxiety and 54.1% had insomnia in Wuhan, China [10]. COVID-19 survivors in other countries have similar psychological status [11–13]. In Ecuador, one of the most affected countries by the COVID-19 pandemic in Latin America, of the 759 confirmed or suspected COVID-19 patients, 20.3% showed moderate to severe depressive symptoms, while 22.5% showed moderate to severe anxiety [11]. In addition, 22.6% and 16.3% of respondents reported clinically concerning levels of psychological impact in Vietnam and the Philippines, the Asian countries with similar cultural context as China [12, 13]. Over time, while the mental symptoms and quality of life of COVID-19 survivors might improve in a certain extent, they are still significantly worse when compared to the rest of the population who did not suffer from COVID-19. Therefore, the psychological impacts of COVID-19 should not be overlooked and should be investigated from the long-term public health perspectives.

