In view of the current epidemic situation and the corresponding prevention and control requirements, internet-based interventions can provide an alternative to face-to-face therapy in enhancing mental health and quality of life for patients with COVID-19. Internet-based healthcare has enabled patients with a variety of geographical distance to receive the same therapy and get benefits from the same interventions, such as digital cognitive behavioural therapy for insomnia [14–16]. This form of psychotherapy can provide treatment and intervention efficiently to patients under the requirements of social distancing during the COVID-19 epidemic [14]. Mindfulness-based intervention (MBI) is an approach that focuses on the cultivation of conscious awareness, and orientation towards the present moment with curiosity and openness, which has been shown helpful in the treatment of mental health [17–20]. Unlike behavioral therapy, which involves relaxation techniques and changing the schedule of daily activities, mindfulness-based interventions help patients cope with anxiety and depression by enhancing their ability to manage stress and reducing negative coping behaviors, hence are more adaptive and persistent [20]. Especially when combined with the web-based technology, mindfulness-based intervention can benefit patients who are infected and treated in isolation wards, and those who are quarantined with no access to psychotherapy as well. [17, 20] An internet-based integrated intervention including some mindfulness skills on depression and anxiety symptoms in Chinese patients with COVID-19 has demonstrated that patients of the intervention group exhibited significantly decreased levels of depression and anxiety symptoms in comparison with those of the control group over a 2-week study period [18].

In the mainland of China, WeChat App and its small programs have dominated the browsing time of mobile phone users [21] Given the emerging need for psychological rehabilitation among COVID-19 survivors recently, this randomized controlled trial will be conducted in this population to examine the effectiveness and feasibility of a 6-week Mindful Living With Challenge (MLWC) intervention focusing on mental health and quality of life via WeChat. We hypothesized that the training could enhance the physical and mental health at post-program and 3-month follow-up.

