## Methods/design

### Study design

This is a prospective, randomized, parallel-group, double-blind, blank controlled trial involving an online 6-week MLWC intervention with a 3-month follow-up. More than 1600 COVID-19 survivors over 18 years old will be randomized to: (1) intervention group: this group will receive a baseline questionnaire followed by a 6-week web-based MLWC intervention, and two questionnaire surveys at post-program and 3 months after the intervention, or (2) waitlist control group: participants in this group will receive three questionnaire surveys conducted simultaneously with the intervention group, and start the same intervention after a 3-month waitlist period (Fig. 1). This study protocol is reported in accordance with SPIRIT reporting guidelines [22]

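### Within-arm paired t-tests are planned as significance tests with no limit on what they may support, and no between-arm contrast is named after baseline

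*Protocol article*

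**What the plan says.** All references are to the protocol article.

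- **Statistical analysis, within-arm test:** the paired-samples t-test "will be used to test for within-group differences". The section does not call this descriptive, and it does not say which variables or time points are paired.
- **Statistical analysis, significance rule:** "two-sided with *P* < 0.05 will be considered statistically significant". No analysis is exempted.
- **Statistical analysis, outcome comparison:** "The repeated measures ANOVA will be used to compare the scores for the six instruments". No group-by-time term or between-arm contrast is named. In this section, differences between groups are mentioned only for the baseline comparison by Student's t-test and chi-square test.
- **Study design:** there is a concurrent waitlist arm, and "participants in this group will receive three questionnaire surveys conducted simultaneously with the intervention group".
- **Background, natural course:** "while the mental symptoms and quality of life of COVID-19 survivors might improve in a certain extent". No size is given, and the same sentence adds that survivors remain worse off than people who did not have COVID-19.
- **Background, hypothesis:** "We hypothesized that the training could enhance the physical and mental health at post-program and 3-month follow-up". This is not worded as a difference between arms.

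**The concern.** The trial asks whether MLWC does better than waiting. Only the comparison of randomised arms answers that. A paired test in the MLWC arm asks whether scores moved from zero change, and they can move through recovery, through repeated completion of the same questionnaires, or through the intervention. The test cannot tell these apart.

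The surrounding text makes a misreading easier. Of the planned tests on post-baseline scores, the paired test is the only one whose comparison is spelled out, and it is the one that ignores randomisation. The hypothesis, as worded, would appear to be met by improvement in the MLWC arm alone. At this sample size even a small shared improvement is likely to be significant. A report could then offer a within-arm P value, or the pattern of significance in MLWC and not in the control, as evidence of efficacy. Neither is a test of the difference between arms.

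**Working it through.** **1. Sample size per arm.** The Sample size section gives 1600 in total, 1:1 allocation and 40% attrition.
- Randomised per arm: 1600 / 2 = 800.
- Remaining if the whole attrition allowance is used: 800 × (1 − 0.40) = 480.

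The 1600 itself cannot be confirmed, because the reference rate or SD behind the 10% margin is not given. It is attainable: 40% versus 30%, power 0.90, two-sided 0.05, needs 477 per arm, and 2 × 477 / 0.6 = 1590. A standardised difference of 0.21 gives the same 477 and 1590. The check below uses only the 480 and the 800.

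**2. Assumptions not in the document.** MLWC has no effect. Both arms improve by the same d, in baseline SD units. The pre/post correlation ρ is 0.5, with 0.6 and 0.7 as alternatives. SDs are equal at the two times.

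**3. Formula.** The mean change in units of the SD of change is dz = d / √(2(1 − ρ)). At ρ = 0.5 the divisor is 1, so dz = d. The probability that the paired test is significant is approximately

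Φ(dz√n − 1.96) + Φ(−dz√n − 1.96).

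**4. Results at n = 480 (√480 = 21.91), ρ = 0.5.**

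| Recovery d | dz√n | P(paired test significant in MLWC arm) |
|---|---|---|
| 0.05 | 1.10 | 20% |
| 0.10 | 2.19 | 59% |
| 0.15 | 3.29 | 91% |
| 0.20 | 4.38 | 99% |

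An observed mean change of about 0.09 SD of change is enough to reach P < 0.05.

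**5. Sensitivity.**
- ρ from 0.5 to 0.7, n = 480: 20–29% at 0.05 SD, 59–81% at 0.10, 91–99% at 0.15, and at least 99% at 0.20.
- n = 800 (no attrition), ρ = 0.5: 29%, 81%, 99% and about 100% for the same four recoveries.

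**6. Between-arm test on the same null trials.** This used 4000 simulated trials for each recovery size, 480 per arm, ρ = 0.5.

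| Shared recovery | Paired test significant, MLWC arm | Between-arm difference in change significant | Significant in MLWC only |
|---|---|---|---|
| 0.10 SD | 59% | 5.0% | 24% |
| 0.20 SD | 99% | 4.7% | 0.8% |
| 0.30 SD | 100% | 4.1% | 0% |

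The 24% agrees with direct arithmetic: 0.591 × (1 − 0.591) = 0.242. The reverse pattern, significant in the control only, is equally likely by symmetry. The between-arm test stays near 5% whatever the shared recovery.

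**The case against.** The strongest reply is that nothing in the article makes the paired tests the test of efficacy. The abstract says differences between the MLWC and control groups will be assessed, the Sample size section frames the trial as superiority over control, and the sentence that plans the paired test opens with the repeated measures ANOVA. Ranking analyses as confirmatory or supportive is also commonly left to a SAP, which is not shown. This stands as far as it goes: between-arm intent is clear, and the absence of a ranking alone would be no finding. What remains is a stated choice, namely significance tests of within-arm change under an unrestricted 0.05 rule.

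Four stronger readings are tempting, and the document does not support them.

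- **That the protocol expects recovery, so the tests would be significant with no effect.** The Background says only that improvement might occur and gives no size. At 0.05 SD the chance is 20–29%.
- **That the type I error of the paired test rises to 59% or more.** Its null hypothesis is zero change. If scores truly change, rejecting is correct, and the percentages are power.
- **That the same argument condemns the analysis planned** "to test the associations between variables in pre-program and post-program in each group". A correlation is unchanged when every score shifts by the same amount, so neither the argument nor the arithmetic applies to it.
- **That the paired tests are planned on all six scales.** The number six belongs to the ANOVA; the variables for the paired tests are not specified.

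**Conclusion.** The point holds as a risk of misinterpretation built into a stated analysis. It does not show that the trial would reach a false conclusion. With equal recovery in both arms and no MLWC effect, the MLWC-arm paired test would be significant in about 20%, 59%, 91% or 99% of trials for recovery of 0.05, 0.10, 0.15 or 0.20 SD, while a between-arm test of change would stay near 5%. The figures rest on an assumed recovery size, an assumed pre/post correlation of 0.5 and the full 40% attrition. A higher correlation or less attrition raises the percentages that are not already near 100%.

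A significant within-arm change becomes false evidence of efficacy only if it is read as a treatment effect. The plan does not say it will be read that way, but nothing in the analysis section prevents it. The change is worth making because it is cheap and the P values it removes cannot answer the trial's question.

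**What to change.** In the Statistical analysis section:

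1. Replace the paired-samples t-tests with a descriptive report of each arm's mean change and its SD, without significance tests. A 95% confidence interval for within-arm change excludes zero exactly when the paired P value is below 0.05, so adding one would bring the same test back in another form.
2. State that efficacy is judged only on the between-arm difference at post-program and at 3 months, adjusted for the baseline score.

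Baseline scores are already collected on every outcome scale (Table 1), so no data are added. The adjustment also helps precision. With equal SDs and ρ = 0.5, the variance factor is 1 − ρ² = 0.75 for the baseline-adjusted comparison, against 2(1 − ρ) = 1.00 for a comparison of change scores.

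The cost is a wording change and the loss of within-arm P values from the report. The per-arm correlation analyses can stay as they are.

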## Discussion

With the unprecedented global health challenge the COVID-19 pandemic has created, the secondary crisis of mental health problems occurred with the outbreak cannot be ignored in a very long period of time. As of March 22, 2021, there are 97 716 COVID-19 survivors cured and discharged from hospital in China, about one-third of them (i.e. 32 572 patients) may be suffering from mental illness as reported by the survey results in Wuhan, China [3, 10]. Prolonged exposure to stressful hospitalization, complex medical examination procedures, and worries about the difficulty of returning to normal life can lead to long-term psychological harm [44]. This will undoubtedly affect the normal operation of many families and bring huge health and economic pressure to the country. Therefore, appropriate innovative mental health support with social distancing merit is warranted to be implemented during the COVID-19 pandemic and its aftermath.

This article describes the design and content of a parallel-group randomized controlled trial (RCT). Our study is the first large sample size study to explore the effect and underlying mechanism of the online MLWC intervention aiming to improve mental health and quality of life among COVID-19 survivors in China. If the study demonstrates that the web-based MLWC is efficacious in such improvement, this user-friendly and convenient mode of mental health intervention would be valuable to treat psychological symptoms and improve their quality of life among COVID-19 rehabilitation patients. The intervention materials also have the potential to be utilized in other populations in various similar situations.

Although previous studies showed that face-to face mindfulness practices are effective to alleviate mental and physical symptoms including depression and sleeplessness [17–19, 45], the web-based mindfulness intervention were proved to have potential in improving the mental health of various study population with more feasibility and acceptability [46]. Currently, the WeChat App and its small programs have become an integral part of everyday life for the majority of the population in China [21]. To ensure the efficacy and the quality of the mindfulness intervention, the content of the intervention course will be developed by a team with clinical psychology background and delivered by a psychiatrist with mindfulness training qualification. Also, to enhance the adherence of the mindfulness-based intervention, professionals in information technology will design the specific small program for managing the questionnaire collection and distribution of the embedded video and audio courses during the study period.

The evaluation of the online MLWC intervention proposed in this study for the treatment of psychological symptoms among COVID-19 survivors is scarce in the international literature. The current study will use RCT, double-blind, evidence-based meditation design, and a longer period of intervention and follow-up, which may ensure more solid conclusions compared to similar studies [18, 47]. Moreover, since some studies have found that the mindfulness intervention did not affect all of the mindfulness facets [48, 49], we will explore 12 sessions of the MLWC intervention as intermediaries on the outcome measures, to determine which sessions have the greatest impact on the outcome, and provide more solid evidence for future psychological interventions. Furthermore, given the inexpensive and portable features of the online MLWC intervention, it can be more easily implemented in harder-to-reach but internet-accessible populations. However, it should be noted that, this study will mainly use questionnaires to measure psychiatric symptoms and do not make clinical diagnosis through structured clinical interview and functional neuroimaging, which may result in measurements that are inconsistent with clinical examinations [50, 51].

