### Study objectives

The primary study objective of this study is to assess the efficacy of the MLWC intervention on PTSD, depression, and anxiety among COVID-19 survivors. The secondary study objective is to investigate the effects of the MLWC intervention on fatigue and sleep quality among COVID-19 survivors. The exploratory objective is to determine how mindfulness training affects mental health and quality of life among COVID-19 survivors and to evaluate the possible mediators and moderators (mindfulness, stillness, nonattachment, resilience and perceived social support) of the link between the MLWC intervention and target outcomes.

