### Randomization and blinding

Participants who meet the eligibility criteria will be randomly assigned (in a 1:1 ratio) to the online MLWC intervention group or waitlist control group. They are supposed to provide informed consent by clicking the ‘I agree to join in the research’ button on the electronic details page of the study. After that, a Quick Response (QR) code will pop up on the page. By scanning this code, participants will be randomly assigned to the intervention or control group (in a 1:1 ratio) by computer-generated numbers. The trial will blind all people who might influence the outcome assessments, including the participants, data analysts, and outcome assessors. Before the trial, the principal investigator of the project will organize training on the randomization procedure and ensure that each research staff is clearly aware of their responsibilities.

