### Intervention

#### The mindful living with challenge (MLWC) intervention

Participants in the intervention group are required to follow the developed WeChat small program by scanning the QR code, and then receive the online MLWC intervention. The MLWC intervention will be developed by two psychiatrists, and one of them has been certified in the Training of Mindfulness Facilitation program at the Mindful Awareness Research Center of University of California, Los Angeles (UCLA). The MLWC intervention adopts some elements from mindfulness-based stress reduction and Mindful Awareness Practices, and includes mindfulness meditation and mindful stretching as core components. A similar intervention has been successfully used on attention monitoring and acceptance in pregnant women in China [19]. Through a series of mindfulness training courses, participants are hypothesized to increase their ability to regulate their emotions and learn to observe the physical pain and psychological frustration caused by COVID-19 infection with equanimity. The purpose of the study is to help participants improve their skills in coping with psychological symptoms, improve their quality of life during recovery, and prepare to return to a normal life.

The MLWC intervention will involve internet-based mindfulness training conducted in six weekly courses of two sessions a week and 0.5 h per session, which focus on the four important parts of MBI: attention control, self-awareness, acceptance and discernment, and relating to difficult thoughts/emotions. Two new sessions of online lessons will be updated weekly in six weeks. The study participants are expected to spend an average of 1 h per week viewing each lesson, which consisted of a theoretical instrument, some meditation practices, and homework in the form of audio and video. Participants will be required to perform formal/informal mindfulness practice at home for 5 min daily initially, advancing to 20 min daily at the end of the intervention period, and to record or report their difficulties and progress during the practice. To enhance adherence, push notifications from the WeChat small program will be sent to participants daily to remind them about their weekly attendance and regular practice. See Table 2 for the context of the MLWC intervention.

**Table 2 Tab2:** The content of mindful living with challenge (MLWC) intervention

Session	Theoretical instrument	Meditation practice	Homework

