#### Control group

Participants in the waitlist control group will receive the full 12-session online MLWC intervention upon completion of all treatment procedures by the intervention group after the 3-month follow-up survey.

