### Data collection, management, and monitoring

Data will be collected at baseline (one week before the intervention), post-intervention (one week after the last session of MLWC), and at 3-month of follow-up. The questionnaire comprises structured and open-ended questions about mental health status, quality of life, and satisfaction with the program. Demographics will be collected at baseline, including age, employment status, education level, marital status, and other information.

Electronic questionnaires powered by the REDCap software will be used to collect data, hence there will be no formal data monitoring committee. Survey questions filled up by the participants will be automatically uploaded to the read-only web-based database to ensure the authenticity of the data. Moreover, our researchers will promptly check the collected data after each questionnaire survey.

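### The Discussion promises to find which of the 12 sessions matters most, but the design has no contrast between sessions beyond participants' own choice to attend

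*Protocol article*

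**What the plan says.** The session aim appears in the Discussion of the protocol article, where the trial is to "explore 12 sessions of the MLWC intervention as intermediaries on the outcome measures, to determine which sessions have the greatest impact" on the outcome. The same sentence presents the answer as stronger evidence for designing later interventions.

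Other sections fix what the design can show:

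- **Randomization and blinding:** participants are "randomly assigned (in a 1:1 ratio) to the online MLWC intervention group or waitlist control group". Nothing below the level of the programme is randomised.
- **Intervention section:** "Two new sessions of online lessons will be updated weekly in six weeks". This is one schedule for the whole arm.
- **Control group:** the waitlist arm receives the programme "upon completion of all treatment procedures by the intervention group after the 3-month follow-up survey".
- **Data collection, management, and monitoring:** surveys are taken at baseline, "post-intervention (one week after the last session of MLWC), and at 3-month of follow-up". Table 1 schedules every outcome and candidate mediator at these three waves and at no other time.
- **Adherence:** the platform logs which sessions each participant opens and the weekly time spent practising.

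Study objectives classes the mechanism work as exploratory and does not list a ranking of sessions. Statistical analysis describes no session-level analysis.

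**The concern.** To say which session has the greatest impact is to make a causal comparison between components of one package. That needs some participants to receive a component, or receive it at a different point, for reasons unrelated to their outcome. Alternatively, it needs enough measurement along the way to adjust for those reasons. Here the package is delivered whole and in one order, and symptoms are not scored while it runs.

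At stake is a conclusion that others may act on. A later programme could be shortened or reordered around the session that appeared most effective, when that session may only mark the participants who were still engaged in that week. The randomised comparison of the primary outcomes is not affected.

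**Working it through.** The plan gives no figure for this aim, so there is none to reproduce. The check is mainly one of identification, followed by an illustration of size.

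**1. What the randomised comparison identifies.** Let Z be the arm (1 = MLWC, 0 = waitlist) and A_k be attendance at session k, for k = 1 to 12. Suppose the outcome is

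Y = α + β_1·A_1 + … + β_12·A_12 + error.

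Controls have A_k = 0 for every k. If everyone in the intervention arm attends everything, A_k = Z for every k, and the model reduces to

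Y = α + (β_1 + … + β_12)·Z + error.

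Only the sum of the session effects can be estimated, and that sum is the effect of the programme. There are 12 × 11 / 2 = 66 pairs of sessions, and none is compared by randomisation.

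**2. What imperfect attendance adds.** Individual β_k become estimable only when some participants skip sessions, and participants decide that themselves. If people leave and do not return, A_k = 1 exactly when the number of sessions attended is at least k. The coefficient for session k then compares those who stopped at k with those who stopped at k − 1. That mixes the session's content with its place in the sequence, with cumulative dose, and with whatever made people stop. How someone felt after one session may also decide whether they open the next, and no symptom scale is taken at that point to adjust for it.

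**3. How much self-selection to expect.** Sample size allows for 40% attrition. With 1600 randomised 1:1, 1600 × 0.5 × 0.6 = 480 intervention participants would remain. Loss on that scale makes selective non-attendance plausible, although the protocol gives no attendance rate.

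**4. Multiplicity alone.** For 12 independent tests at 0.05, the chance of at least one false positive is 1 − 0.95^12 = 0.46.

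**5. Illustration with self-selection.** The parameters in this step are assumptions, apart from the 480 participants derived above. One engagement trait raises attendance at every session and is correlated 0.3 with outcome. Attendance thresholds fall evenly from 1.3 to 0 on a standard normal scale, which means attendance of about 90% at session 1 and 50% at session 12. Each setting used 2000 runs.

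| Setting | Result |
|---|---|
| No session effect, no confounding: joint 12-session regression flags at least one session | 44% of runs |
| No session effect, confounding 0.3: joint regression flags at least one session | 75% of runs |
| No session effect, confounding 0.3: each session tested alone | rejects in 89% to 99% of runs, depending on session |
| One session truly best (0.10 SD against 0.02 SD for the others), confounding 0.3: joint regression ranks it first | 14% of runs, against 1/12 = 8% by chance |

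The 44% agrees with the 46% in step 4. The rise to 75% is due to self-selection. In the last row, even a session with five times the effect of the others (0.10 / 0.02) is rarely placed first.

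**6. The units to be ranked.** Control group and Discussion refer to 12 sessions, and the intervention section to two a week for six weeks, but Table 2 numbers only six. The article does not describe 12 separate components.

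**The case against.** The best defence is that this is a single sentence in the Discussion, phrased as exploration. It is not among the stated objectives and no session-level analysis is listed. The mechanism aim is exploratory, and analysis detail may sit in a plan that is not shown. It is also untrue that nothing is recorded between sessions: the platform logs attendance and weekly practice time, and participants report difficulties during training. Finally, 0 of 66 pairs restates the lack of randomisation and does not measure bias.

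Much of this stands, and it lowers the severity. It does not rescue the sentence, which goes beyond exploring to determining which sessions have most impact. No analysis plan can supply session-level randomisation or symptom scores between sessions. Log-ins and practice time are the self-selected exposure itself, and participant feedback is not an outcome scale.

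A reader might go further and infer that the mediation and moderation analyses fail too. The documents do not support that, for these reasons:

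- **Timing.** The plan will use "hierarchical multiple regression analyses to test how or why some facets of mindfulness may take a role in our outcomes", but does not say which waves enter the model. A same-time regression would be a guess.
- **Within-arm correlations.** The "correlation analysis to test the associations between variables in pre-program and post-program in each group" is listed separately and is not called a mediation analysis.
- **Randomised contrast.** Study objectives speaks of mediators and moderators of the link between the intervention and the outcomes, so the intervention remains the exposure. Nothing shows that the contrast between arms is discarded.
- **Identifiability.** Table 1 measures mediators and outcomes at all three waves. Post-program mediators can be related to 3-month outcomes with baseline adjustment, under the usual assumption of no unmeasured mediator-outcome confounding.
- **Dual roles.** Listing the same constructs as "possible mediators and moderators (mindfulness, stillness, nonattachment, resilience and perceived social support") is no contradiction, since a baseline value can moderate while a later change mediates. A rule that moderators come from baseline is detail an article may leave to the full plan.

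**Conclusion.** The point holds for the session-ranking claim and for nothing wider. As designed, the trial can estimate the effect of the whole programme against waitlist. It cannot determine which session has the greatest impact, because session exposure varies only through participants' choices and is tied to order and cumulative dose.

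This conclusion rests on the design facts in the protocol article. It does not depend on the simulation, whose percentages would change with the assumed attendance pattern and the strength of confounding. They show only that spurious session findings could be common: 44% of runs with no confounding and 75% at the assumed 0.3.

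Severity is low. The claim is exploratory, and the primary and secondary efficacy comparisons are unaffected. The mediation and moderation plans are not faulted here.

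**What to change.** In the Discussion, remove the claim that the trial will determine or rank the impact of individual sessions, together with the suggestion that such a ranking would give firmer evidence for later interventions. Say instead that session completion and practice time will be summarised, and that their relation to outcome in the intervention arm will be reported as a descriptive, non-randomised association that can only generate hypotheses. If results are shown by session, state beside them that they are confounded with order, cumulative dose and adherence.

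The cost is a change of wording and the loss of one exploratory deliverable. No data collection, sample size or primary analysis changes.
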